## BACKGROUND AND RATIONALE:

AKI is a common complication in hospitalized patients and is associated with increased risk of hospital readmission, morbidity, mortality and a high cost of care. The estimated annual cost of AKI care in the United States is over 10 billion dollars and with all-cause incidence of AKI continuing to rise, the total cost expenditure around AKI continues to increase. Over this same decade, a consensus definition of AKI, new functional and biochemical biomarkers of renal injury and advancements in electronic health records (EHR) AKI risk models have informed and advanced AKI research. While several of these individual entities have demonstrated promise, most of this work has focused solely on critically ill ICU patients. Despite these advancements, clinicians do not have a systematic tool to reliably determine which patients will develop AKI or which will progress to more severe forms of AKI.

Over the last decade, our investigative group has worked to detect patients at highest risk for the most severe forms of AKI and the most adverse outcomes. Using a multi-center cohort we derived and validated an EHR-based AKI risk assessment model to predict the development of creatinine based AKI *in hospital ward patients* using patient vital signs, labs and demographics (called Electronic Signal to Prevent AKI; ESTOP-AKI). ESTOP-AKI, which is entirely derived from data freely available in the EHR, accurately predicts the future development of stage 3 AKI a median (IQR) of 35 (14-97) hours before any evidence of serum creatinine (SCr)-based AKI with an AUC of 0.83. The University of Chicago (UofC) developed and currently utilizes a pre-existing platform to provide real-time reporting of ESTOP-AKI, as part of a real-time risk assessment scores program for ward-patients at high risk for sepsis, ICU transfer and inpatient cardiac arrest (Electronic Cardiac Arrest Risk Triage (ECART)). Although others have developed AKI algorithms, these investigators have focused on the presences of Stage 1 AKI and thus implementation did not result in improved outcomes. More recently, others have reported similar risk prediction algorithms to predict impending AKI however it remains unclear if these models can be used to improve outcomes. ESTOP-AKI performs on par with these models, accurately predicting Stage 3 AKI 1.5 days earlier than SCr.

AKI is a diverse and complex clinical syndrome, often multifactorial in nature and no single therapeutic intervention is likely to improve outcomes. As such, we propose the intervention be a standardized early nephrology consult (ENC). ENC for AKI has been shown to associate with improved patient outcomes, lower peak SCr, less severe AKI, shorter length of hospital stay (LOS), increased renal recovery post-AKI and reduced morbidity /mortality. In the setting of early AKI, those patients whose physicians complete all components of an AKI care bundle have better outcomes compared to those with partially completed bundles. However these data arise from non-randomized trials. These same studies demonstrate that the average nephrology consultation is called 2 days after there is clinical evidence of AKI (rise in SCr or oliguria) and that 35-50% of AKI patients do not see a nephrologist until 5 days after clinical AKI. Data from the UofC wards (Winter 2017) demonstrate the average AKI consult (n=59) occurs on hospital day 4 after a 1.6 mg/dL increase in SCr from baseline, with 44% of patients having AKI  $\geq$  Stage 2 AKI.

**Specific Aim** –To perform a prospective randomized clinical trial utilizing the ESTOP- AKI risk assessment model prior to measurable loss of kidney function (“pre-AKI”) to determine if potential benefit (defined as lower peak SCr, lower AKI stage, shorter LOS and less morbidity and mortality) of ENC exists as compared to usual care. High-risk patients identified through ESTOP-AKI (score  $\geq 0.01$ ) will be randomized within 12 hours of consent, to receive a standardized ENC from a UofC nephrology fellow and research protocol specific attending or usual care (SOC). The standardized nephrology consultation will address pre-AKI differential diagnosis, nephrotoxins/drug dosing, volume status/renal perfusion. These specific elements were chosen as the focus of the early intervention based on prior successful AKI care bundles/ guidelines. (Table 3) We hypothesize that high risk subjects receiving early-individualized nephrology-directed pre-AKI care will have improved outcomes (e.g. lower peak SCr, lower AKI stage, shorter LOS, fewer ICU stays and improved post-discharge renal function) compared to those receiving usual care.

**Hypothesis:** We hypothesize that combining the precision medicine approach of ESTOP AKI with early structured real-time individualized nephrology-centered care will improve patient outcomes (as measured by lower peak SCr, less severe AKI staging, fewer ICU transfers, shorter LOS and less mortality).

**Objectives:** The objective of this proposal is to transform the medical care of hospitalized patients at risk for the development of acute kidney injury (AKI) through the utilization of an automated, real-time, electronic medical record risk assessment score allowing for early standardized nephrology focused intervention.

### **ESTOP-AKI DEVICE**

The electronic risk prediction algorithm (ESTOP-AKI) being studied will interface with Epic to determine the likelihood for the patient to develop AKI. The study team is creating the algorithm with the help of software engineers and architects from UofC CBIS. ESTOP-AKI will use the following information from Epic:

- Medical Record Number
- Name
- Age
- Sex
- vital signs (respiratory rate, heart rate, temperature, pulse pressure index, systolic and diastolic blood pressure, oxygen saturation, and mental status)
- laboratory values (complete blood count, liver function panel, and blood chemistries/basic metabolic panel).

Upon generation of a risk level, ESTOP-AKI will electronically notify a member of the study team the eligibility status of the patient.

### **STUDY DESIGN**

**Type of Study:** Single-center Prospective Randomized Interventional Trial

**Duration of Study:** 3 years

**Schedule of Events**

| Event                         | Screening      | Enrollment
(Day 0) | Daily
(Days 1-7) | Hospital
Discharge | Follow Up
(Month 3, 6,9,
and 12) |
|-------------------------------|----------------|-----------------------|---------------------|-----------------------|----------------------------------------|
| Demographics                  | X              |                       |                     |                       |                                        |
| Inclusion/Exclusion           | X              |                       |                     |                       |                                        |
| ESTOP-AKI Risk
Assessment  | X              |                       |                     |                       |                                        |
| Informed Consent              |                | X                     |                     |                       |                                        |
| Blood Collection c |                | X                     | X                   | X                     |                                        |
| Urine Collection c |                | X                     | X                   | X                     |                                        |
| Early Nephrology
Consult   |                | X a        |                     |                       |                                        |
| Chart Review b     | X b | X b        | X b      | X b        | X b                         |
| Follow Up Phone
Calls      |                |                       |                     |                       | X                                      |

**Primary Endpoint Definition** -The primary endpoint of interest,  $\Delta$ -SCr, is the peak change from study entry in SCr level over a 7-day interval. We define  $\Delta$ -SCr as the maximal change in creatinine over this interval, and aim to detect a clinical difference in  $\Delta$ -SCr between the SOC and ENC treatment groups. On average, in patients with an ESTOP-AKI score  $\geq 0.01$  (the enrollment cutoff), the mean change in SCr in a 7-day interval was 0.369, (standard deviation 0.734).

**Secondary Endpoint:** Secondary endpoints include differences by treatment group in the proportion and time to event of patients who a) develop > Stage 2 AKI, b) require RRT, c) undergo ICU transfer, and d) require non-research nephrology consult. The LOS and the distributions of time to peak SCr will also be compared.

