## **STUDY PROCEDURES**

**Screening:** As part of ESTOP-AKI production, the algorithm which assesses risk on a real time basis will be reported in EPIC but not labeled as an AKI risk score. [name] research team will approach eligible patients (and their treating physicians) about study enrollment, utilizing a UofC model in place from prior work by [name] and [name]'s. These pre-emptive and consistent in-servicing of treating physicians/nurses, research staff being omnipresent with dedicated ward-based work space and establishing a dedicated pager/contact numbers for the study with 24 hour coverage.

**Randomization:** Once consented patients will be randomized to ENC or usual care through an on-line RED-CAP based block-randomization schema.

**Study Visits:** Following enrollment, subjects will receive a research ENC on Day 0 and the consultation recommendations will be discussed with the primary team and will be placed in the EHR within 8 hours of enrollment. The research team will be made up of a rotating panel of UofC nephrology attendings specifically trained for this protocol. Following hospital discharge, there will be a 3 month ( $\pm 2$  weeks) follow up phone call.

**Intervention:** The ENC will provide guidance on Differential Diagnosis, Nephrotoxins/Drug Dosing and Volume Status/ Renal Perfusion). The research ENC will have daily follow up with the inpatient team and document recommendations based on these 3 core elements. At any time during the study any patient in either arm can receive a formal non-research based renal consultation at the discretion of the treating physicians and these events will be captured. Once a non-research based consult has been called the patient will no longer be seen by the research team but will still be eligible for data collection, blood and urine and follow up testing. As we anticipate some proportion of patients in both arms will receive non-research consultations we will be tracking how many patients in receive nephrology consultation as well as other diagnostic aspects of AKI care in order to determine the degree of contamination in the usual care arm (see below). **No patient will be denied a non-research based consult at any time.**

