**Analytic Methods - Primary endpoint:** Difference of mean  $\Delta$ -SCr between the ENC and SOC group. Randomized assignment stratified by predicted risk (ESTOP-AKI score) maximizes the potential for equal distribution of potential confounding factors by treatment group. Primary analysis is thus a comparison of means from a 2-factor (treatment and stratification level) ANOVA model. If there is evidence of imbalance in key factors (baseline SCr, age, sex, hospital service type), then a secondary analysis using linear model methods will be conducted to compare adjusted means. For patients who die within 7-days or receive RRT we will analyze the data with  $\Delta$ -SCr set at their maximum SCr prior these events. **Secondary endpoints:** For binary outcomes (i.e., AKI stage, ICU transfer), proportions will be compared between ENC and SOC groups via the binomial test. The primary analysis will be a direct comparison of these proportions. Logistic regression analysis may be conducted to account for covariate imbalances. Time to discharge (LOS) and time to peak SCr distributions will be compared by group using nonparametric statistics for differences in specific

quantiles (e.g. medians) and other summaries (means). These endpoints can also be approached from a survival analysis modeling perspective, with treatment and other covariates investigated in relation to event rates.

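### Length of stay has no rule for in-hospital death, and non-research nephrology consult means different things in the two arms, so neither secondary comparison can be read as benefit as it stands

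*Protocol*

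**What the plan says.** **LOS and time to peak SCr.** The Secondary Endpoint paragraph of the Protocol (under Study Design) says "The LOS and the distributions of time to peak SCr will also be compared". Analytic Methods adds that "Time to discharge (LOS) and time to peak SCr distributions will be compared by group using nonparametric statistics", summarised by quantiles such as the median and by means. It then says "These endpoints can also be approached from a survival analysis modeling perspective", which is an option and not a commitment.

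**Death.** The only rule for death or RRT in Analytic Methods is for Δ-SCr, the primary endpoint. No section says how an in-hospital death enters LOS. Less mortality is part of the Specific Aim and the Hypothesis, but mortality is not named in the Secondary Endpoint paragraph.

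**Consult.** The same paragraph lists patients who "d) require non-research nephrology consult" as a proportion and time-to-event endpoint, in one series with AKI stage, RRT and ICU transfer. Study Procedures (Intervention) gives ENC patients daily research nephrology follow-up. It leaves a non-research consult to the treating physicians in either arm, and stops the research team's visits once one is called. It also tracks consultations "in order to determine the degree of contamination in the usual care arm".

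**The concern.** Shorter LOS is one of the named benefits of ENC. Death ends a stay. If the observed stay of a patient who dies early enters a comparison of medians or means, it counts as a good result, and the arm with more early deaths gains on LOS. A reader of the listed endpoints would not see the deaths behind it.

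The consult endpoint has a different problem. The intervention is itself a nephrology consult, so whether the treating team calls another depends on allocation as well as on the kidneys. Placed beside RRT and ICU transfer, a difference in consult rate invites reading as a clinical effect.

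At stake is the interpretation of two secondary results. The primary analysis is untouched.

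**Working it through.** The plan gives no figure to reproduce here: it states no LOS distribution, death rate or consult rate. The LOS part is illustrated with assumed values, and the other two parts are settled by comparing sections.

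**1. LOS and death (illustration only)**

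Assumed: time to discharge is log-normal with median 7 days and log-SD 0.7; deaths fall on days 1 to 5, hence below the median; a proportion *p* of patients dies. F is the log-normal distribution function and z the standard normal quantile.

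- *Stay cut at death.* All deaths lie below the median m, so p + (1 − p)·F(m) = 0.5, and m = 7·exp(0.7·z[(0.5 − p)/(1 − p)]).
- *Death ranked worst.* All deaths lie above the median, so (1 − p)·F(m) = 0.5, and m = 7·exp(0.7·z[0.5/(1 − p)]).

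| p | z, cut at death | Median, cut at death | z, death worst | Median, death worst |
|---|---|---|---|---|
| 0% | 0 | 7.00 | 0 | 7.00 |
| 5% | −0.066 | 6.68 | 0.066 | 7.33 |
| 10% | −0.140 | 6.35 | 0.140 | 7.72 |
| 15% | −0.223 | 5.99 | 0.223 | 8.18 |

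Take an arm with 10% deaths against one with 5%. Under the first rule its median looks 6.68 − 6.35 = 0.33 day shorter. Under the second it is 7.72 − 7.33 = 0.39 day longer. The sign depends on a rule that the protocol does not state.

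For means, the shift is (difference in death proportion) × (stay of survivors − time to death). With an assumed 8-day stay and death at day 4, this is 0.05 × 4 = 0.2 day for a 5-point difference and 0.10 × 4 = 0.4 day for a 10-point difference.

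**2. Non-research consult (sections side by side)**

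- *Before the event.* An ENC patient already has daily research nephrology advice. A usual-care patient has no nephrology care, since prior renal consultation during the admission is an exclusion criterion.
- *Who decides.* The treating physicians do. Because the ENC recommendations are discussed with the primary team and entered in the record, those physicians know who has a research nephrologist.
- *After the event.* In ENC the research consult stops and a clinical one takes over. In usual care, nephrology care begins.
- *Second use.* Study Procedures also uses consultations to gauge contamination of usual care. The same count is therefore both an outcome and a measure of how far the treatment contrast has been diluted.

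Research advice may replace a clinical consult or prompt one. As an assumed example, let 20% of usual-care patients have a consult (18 of 90). If research follow-up made half of these unnecessary, ENC would show 10% (9 of 90) with no kidney effect. If it prompted consults instead, ENC would show more than 18.

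**3. Time to peak SCr**

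A patient whose creatinine never rises peaks at or near entry, so preventing injury shortens the time. Delaying injury lengthens it. An early peak can thus mean no injury or fast injury, and a late peak can mean delayed or still progressing injury. The protocol names no favourable direction, and the Hypothesis does not mention this variable.

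**The case against.** **LOS.** A reader might infer that the protocol counts an in-hospital death as a short stay. It does not say so; it is silent. The optional survival approach leaves room for proper handling of death, and the statistical analysis plan, which is not at hand, may set the rule. The Secondary Endpoint list is also introduced as inclusive, so mortality may be reported anyway. Nor does the problem necessarily flatter ENC: if ENC lowers mortality, as hypothesised, stays cut at death would work against it. All of this stands, and it limits the point to an unguarded method. What remains is that the comparison actually described is one of raw medians and means, while the survival approach is optional and silent on death.

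**Consult.** Consults appear in neither the Specific Aim's definition of benefit nor the Hypothesis, and Study Procedures already treats them partly as contamination. A reader might also infer that ENC mechanically lowers the consult rate; the documents do not establish that direction. What remains is the listing beside RRT and ICU transfer, which gives the event an outcome role that a choice of test cannot repair.

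**Time to peak SCr.** A reader might infer that this endpoint can favour the wrong arm. With no direction of benefit it cannot favour either; it is simply hard to interpret. A descriptive comparison needs no direction. No replacement is called for, because time to the AKI-stage event is already a listed endpoint.

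**Conclusion.** The point holds in limited form. As described, the LOS comparison has no protection against early death appearing as a good result, and the listed endpoints do not include mortality to show it. Non-research consult has an arm-dependent meaning, so a difference in either direction need not reflect kidney outcome. Time to peak SCr is descriptive only.

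The effect is confined to secondary endpoints and is probably modest. Under the assumed inputs the LOS distortion is about 0.2 to 0.4 day for a 5- to 10-point difference in deaths, and it shrinks towards nothing when few patients die. These figures rest wholly on assumed stays, death times and death rates; the real size cannot be computed from the documents. The documents do not support a claim that the trial's main conclusion is at risk, or that the distortion runs in ENC's favour.

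**What to change.** - **LOS.** Define it as time from randomisation to discharge alive. Treat in-hospital death as a competing event (cumulative incidence by arm) or assign it the worst rank in a rank comparison. Report in-hospital mortality by arm beside it.
- **Non-research consult.** Report it by arm as a process and contamination measure, not as evidence of efficacy.
- **Time to peak SCr.** Label it descriptive, and leave the AKI-stage time-to-event endpoint to carry the question of timing.

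The cost is a change of wording in the protocol or analysis plan. Discharge and death should be obtainable from the chart review already scheduled at discharge, and consults are already captured. The downside is that one listed endpoint becomes descriptive. The primary analysis and sample size do not change.

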**SUBJECT SELECTION AND WITHDRAWAL**

**Number of Subjects:** 180 patients admitted to UofC Hospital over a 24 month period (90 per arm)

**Inclusion Criteria**

- a) Age >18 years old
- b) Initial E-STOP AKI score  $\geq 0.01$  within the last 12 hours.

**Exclusion Criteria**

- a) Voluntary refusal or missing written consent of the patient / legal representative.
- b) Patients with a known history of end-stage renal disease on dialysis (including renal transplantation).
- c) Patients without a measured serum creatinine value during their inpatient stay.
- d) Patients with a creatinine >4.0 mg/dl at the time of admission or available in the EHR from the last 6 months
- e) Patients with prior episode of KDIGO defined AKI during this same hospitalization- regardless of E-STOP AKI score
- f) Patients with prior renal consultation during their admission.

**Location:** All research activities will take place at the University of Chicago Medical Center. Data will not be shared outside the institution or with investigators outside the study team. De-identified

data may be placed into NIH databases, such as dbGaP, as this is a NIH-funded study. Security measures are in place to protect these data

**Informed Consent Process** The investigator will make certain that an appropriate informed consent process is in place to ensure that potential research subjects, or their authorized representatives, are fully informed about the nature and objectives of the clinical study, the potential risks and benefits of study participation, and their rights as research subjects. The investigator, or a sub-investigator(s) designated by the sponsor-investigator, will obtain the written, signed informed consent of each subject, or prior to performing any study-specific procedures on the subject. The date and time that the subject signs the informed consent form and a narrative of the issues discussed during the informed consent process will be documented in the subject's case history. The investigator will retain the original copy of the signed informed consent form, and a copy will be provided to the subject.

The investigator will make certain that appropriate processes and procedures are in place to ensure that ongoing questions and concerns of enrolled subjects are adequately addressed and that the subjects are informed of any new information that may affect their decision to continue participation in the clinical study. In the event of substantial changes to the clinical study or the risk-to-benefit ratio of study participation, the sponsor-investigator will obtain the informed consent of enrolled subjects for continued participation in the clinical study.

## **STUDY PROCEDURES**

**Screening:** As part of ESTOP-AKI production, the algorithm which assesses risk on a real time basis will be reported in EPIC but not labeled as an AKI risk score. [name] research team will approach eligible patients (and their treating physicians) about study enrollment, utilizing a UofC model in place from prior work by [name] and [name]'s. These pre-emptive and consistent in-servicing of treating physicians/nurses, research staff being omnipresent with dedicated ward-based work space and establishing a dedicated pager/contact numbers for the study with 24 hour coverage.

**Randomization:** Once consented patients will be randomized to ENC or usual care through an on-line RED-CAP based block-randomization schema.

**Study Visits:** Following enrollment, subjects will receive a research ENC on Day 0 and the consultation recommendations will be discussed with the primary team and will be placed in the EHR within 8 hours of enrollment. The research team will be made up of a rotating panel of UofC nephrology attendings specifically trained for this protocol. Following hospital discharge, there will be a 3 month ( $\pm 2$  weeks) follow up phone call.

**Intervention:** The ENC will provide guidance on Differential Diagnosis, Nephrotoxins/Drug Dosing and Volume Status/ Renal Perfusion). The research ENC will have daily follow up with the inpatient team and document recommendations based on these 3 core elements. At any time during the study any patient in either arm can receive a formal non-research based renal consultation at the discretion of the treating physicians and these events will be captured. Once a non-research based consult has been called the patient will no longer be seen by the research team but will still be eligible for data collection, blood and urine and follow up testing. As we anticipate some proportion of patients in both arms will receive non-research consultations we will be tracking how many patients in receive nephrology consultation as well as other diagnostic aspects of AKI care in order to determine the degree of contamination in the usual care arm (see below). **No patient will be denied a non-research based consult at any time.**

**Blood, and urine collection:** We will collect up to 10 ml of blood and 20ml of urine from each recipient at daily for the first 7days. Samples will be promptly centrifuged, aliquoted and will be stored at -80°C as previously described. Samples will be used to measure SCr and electrolytes should they not be measured clinically on a given day. Excess samples will be bio-banked for future biomarker (biochemical and genetic) investigation to determine if novel tests may guide clinical care in patients at high risk for severe AKI per E-STOP-AKI. Any shared samples would be de-identified prior to transfer; no clinical data will accompany the samples.

De-identified biobanked samples will be shared with external collaborators, including Sphingotec GmbH, for advanced biomarker analysis. These analyses will focus on the evaluation of proenkephalin and other novel biomarkers to enhance the prediction and management of AKI.

**Data to be collected:** We will systematically retrieve pre-determined variables for each participant, including demographics (age, gender, race), comorbidities (reason for hospitalization, AKI risk factor, severity of illness, diabetes, CHF, COPD, hypertension, pre-enrollment renal function and medication profile), operative variables (e.g. cardiopulmonary bypass time, transfusions, hypotension), hospital prescribed medications (vaso-active medications, ACE-I, ARBs, nephrotoxins). Vital signs, fluid balance and urine output for days 1-7 will be recorded. Data will be entered into a pre-established online secure password protected REDCAP database. Data integrity will be checked with 5% random accuracy models.

